### Participants

#### Sample Size Calculation

This study is exploratory, since, to our knowledge, no other study has used the OSS to predict manifest sleepiness. Thus, because no data would allow us to statistically determine the number of participants required, this number has been arbitrarily set to 40 healthy volunteers. We believe this number will facilitate preliminary exploration at both inter- and intraindividual levels with an appropriate protocol.

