### Experimental Session 1: Fragmented Sleep

This session lasted for 3 consecutive nights and days, during which sleep was recorded. In order to induce sleep pressure on day 3, the third night was fragmented (with 2 imposed wake-ups, during which attentional and vigilance tests were carried out). Three blocks of behavioral tests were conducted during the third day (Figure 1A). One block of tests is 4 hours long and includes, in a fixed order, a driving simulation, cognitive tests, evaluation of sleep pressure, and self-assessments of drowsiness and mind-wandering, while continuous EEG is recorded (Figure 2).

The detailed schedule of days and nights is organized as follows:

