### Data Analysis

#### Statistical Analysis

The analyses will be performed using R version 4.4.2 (R Foundation for Statistical Computing) and IBM SPSS Statistics version 27 (IBM Corp) software for Windows. The normality of the data will be assessed using the Shapiro-Wilk normality test, the equality of variance will be evaluated with the Levene test, and the sphericity of the data will be checked using the Mauchly test. Continuous variables will be expressed as means and categorical variables as proportions (%). *P* values less than .05 will be considered statistically significant.

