#### Predictive Models Using Resting State EEG

To predict drowsiness-mediated behavioral performance, the proposed model leverages resting-state EEG recordings obtained prior to task execution. The primary behavioral end point is SDLP, which is dichotomized into 2 classes: “Good Performance” and “Poor Performance” based on the 33rd and 66th percentiles of the SDLP distribution. This percentile-based approach ensures approximately balanced class sizes, and the resulting thresholds and participant categorizations were validated by domain experts.

Considering the nonstationary nature of EEG signals and their susceptibility to interindividual variability, machine learning methods capable of handling such variability will be prioritized. Feature extraction and selection will be guided by SHAP (Shapley Additive Explanations) values computed on the training set. Channels and features with high importance will be selected and then evaluated on a separate validation subset within each fold. Performance will be reported on a completely unseen test set to prevent leakage.

A leave-one-subject-out cross-validation strategy will be applied to provide a robust evaluation under intersubject variability. Within each fold, to optimize hyperparameters and feature selection, a nested validation set will be defined by randomly selecting a subset of participants from the training pool (ensuring no overlap with the test participant). All preprocessing, feature selection, and hyperparameter tuning will be performed exclusively on the training and validation subsets, with the test participant held out to avoid information leakage.

Classification will be performed using CatBoost, an ensemble-based gradient boosting algorithm suitable for tabular and heterogeneous data. To enhance generalizability and benchmark the findings across distinct algorithmic frameworks, additional classifiers, including radial basis function support vector machine, decision trees, logistic regression, and extreme gradient boosting, will also be applied. Demographic and behavioral covariates (eg, age, gender, chronotype, daydreaming frequency, and sleep history) will be optionally included to account for residual interindividual variability.

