Model performance will be evaluated using accuracy, precision, recall, and *F*_1_-score, reporting both macroaveraged and weighted-averaged metrics to account for potential class imbalance. Comparing these metrics allows assessment of classifier sensitivity to imbalanced classes. Bootstrapping and permutation testing will be applied to evaluate the statistical significance and robustness of the results, ensuring that predictive performance is not due to chance.

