### Resting-State EEG Predictive Advantage

Unlike conventional automatic drowsiness detection systems that identify spontaneous drowsiness or related performance declines in real-time —often too late to prevent impairments or accidents— our approach might predict drowsiness-induced performance deterioration in advance, enabling timely intervention with effective countermeasures to prevent functional decline. The aim is to assess the cognitive readiness and forecast the likelihood of either good or impaired performance before the task.

Like certain algorithms, we will leverage machine learning analyses while integrating interindividual characteristics, such as age, sex, chronotype, and accumulated sleep deprivation. This personalized approach aims to enhance predictive accuracy.

By leveraging automatic sleep pressure quantification through resting-state EEG data—adjusted for interindividual characteristics— our study will provide valuable insights into individuals’ vulnerability to drowsiness before critical lapses in attention or vigilance occur. This predictive capability enables proactive interventions, such as fatigue management strategies, to prevent performance deterioration and reduce the risk of accidents.

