### Implications for the World of Work and Transport

The ability to forecast drowsiness-related impairments has significant applications in occupational and transport settings [5,62-64]. Workers in industries requiring night shifts, such as in health care, emergency response, and manufacturing, frequently experience sleep deprivation, which can lead to decreased cognitive performance and increased accident risks at work [5,65,66]. By integrating predictive drowsiness assessment tools, employers can enhance safety measures through “fatigue” monitoring and targeted interventions to prevent fatigue-related errors and accidents.

The transport sector, particularly aviation, rail, and road transport, is highly vulnerable to drowsiness-related accidents [67]. Microsleeps and lapses in vigilance can have catastrophic consequences, making early prediction of drowsiness essential for safety. Unlike real-time systems that detect spontaneous drowsiness only at the moment it occurs, our approach will offer a preemptive strategy by identifying individuals at risk of performance decline related to drowsiness beforehand. In other words, our approach systematically evaluates an operator’s cognitive readiness and forecasts the probability of optimal or impaired performance due to sleepiness prior to the initiation of a driving task, flight, or other transportation activity. Our EEG-based drowsiness detection systems can facilitate the implementation of drowsiness-monitoring technologies in pilots, train operators, and long-haul drivers, significantly reducing the likelihood of sleep-related incidents occurring. Additionally, our findings could inform regulatory policies mandating proactive drowsiness risk management in safety-sensitive professions.

Continuous real-time drowsiness assessment is essential, especially for validating Driver Drowsiness Warning systems in advanced driver-assistance systems. To detect spontaneous drowsiness during driving or work scenarios, we will develop an automated algorithm that analyzes 2 EEG channels in accordance with OSS scoring.

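### The resting-EEG predictor is scored only on Good/Poor calls, so the forecast probability claimed in the Discussion is never evaluated, and a chance test built on those calls would lose some power

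*Protocol article*

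**What the plan says.** The section *Predictive Models Using Resting State EEG* turns the standard deviation of lateral position (SDLP) into Good and Poor classes "based on the 33rd and 66th percentiles of the SDLP distribution". Several classifiers are fitted with leave-one-subject-out cross-validation. On scoring it says "Model performance will be evaluated using accuracy, precision, recall, and" the F1 score, each macro- and weighted-averaged. It then adds: "Bootstrapping and permutation testing will be applied to evaluate the statistical significance and robustness of the results". It does not name the statistic that is permuted, the unit of permutation or the sidedness. The *Statistical Analysis* section gives only the general rule that P "values less than .05 will be considered statistically significant".

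The Discussion describes the product in other terms. *Resting-State EEG Predictive Advantage* states the aim to "forecast the likelihood of either good or impaired performance before the task". *Implications for the World of Work and Transport* says the approach "forecasts the probability of optimal or impaired performance due to sleepiness prior to the initiation of a driving task". The article mentions no AUC, Brier score, log loss or calibration measure.

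**The concern.** CatBoost, extreme gradient boosting, logistic regression and decision trees all return a probability of Poor performance. Every listed metric is computed after that probability has been replaced by a class, so a forecast of 51% and one of 99% count the same. The planned evaluation therefore cannot show whether the probabilities are right, or whether higher forecasts go with worse drives at any cut-off other than the one used. Prediction from resting EEG is one of the study's two main objectives. A reader of the results could take good accuracy as support for a probability forecast that was never tested.

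There is a second, conditional consequence. If the permutation test uses accuracy or F1, it discards ranking information that the predictions already hold. The sample gives little room for that: "this number has been arbitrarily set to 40 healthy volunteers".

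**Working it through.** The article states no effect size, power, target accuracy or AUC for this objective, so there is no figure to reproduce. The inputs below come from the article unless marked as assumed.

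**1. Can the listed metrics see a wrong probability?** A call is Poor when the predicted log-odds exceed 0. Multiplying all log-odds by a positive constant c changes no sign, so no call changes, and accuracy, precision, recall and F1 are all unchanged. Simulated example (assumed: normal scores, equal classes, means 0.8 SD apart):

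| c | Accuracy | F1 | Brier score | Mean forecast among drives called Poor | Observed share Poor among them |
|---|---|---|---|---|---|
| 0.3 | 0.656 | 0.656 | 0.230 | 0.551 | 0.656 |
| 1 | 0.656 | 0.656 | 0.215 | 0.655 | 0.656 |
| 3 | 0.656 | 0.656 | 0.245 | 0.816 | 0.656 |
| 6 | 0.656 | 0.656 | 0.281 | 0.898 | 0.656 |

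A constant forecast of 0.5 has a Brier score of 0.25. At c = 6 the probabilities are worse than that, yet accuracy and F1 do not move. AUC does not change under this rescaling either, so a proper score is needed as well as a ranking measure.

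**2. How many scored units?** Session 1: "Three blocks of behavioral tests were conducted during the third day". Session 2 has six blocks and then three more. Each block holds one drive, so there are 3 + 6 + 3 = 12 per participant and 40 x 12 = 480 in all. If the middle third is dropped (a reading, since the text does not say so), about 480 x 2/3 = 320 drives remain. If participants are the unit, about 40 x 2/3 = 26 to 27 remain.

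**3. Power, asymptotic case.** For normal scores cut at the ideal point, the efficiency of calls is 2/pi = 0.64 and that of ranks 3/pi = 0.955, a ratio of 2/3. So power on accuracy = Phi[(z_alpha + z_AUC power) x sqrt(2/3) - z_alpha]. At one-sided 5% and 80% AUC power: (1.645 + 0.842) x 0.816 - 1.645 = 0.385, and Phi(0.385) = 0.65.

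| Power of AUC test | Accuracy, one-sided (loss) | Accuracy, two-sided (loss) |
|---|---|---|
| 0.60 | 0.46 (14 points) | 0.44 (16) |
| 0.70 | 0.55 (15) | 0.53 (17) |
| 0.80 | 0.65 (15) | 0.63 (17) |
| 0.90 | 0.77 (13) | 0.75 (15) |

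**4. Power, simulated permutation tests, one-sided 5%.**
- 160 independent drives per class, accuracy against AUC: true AUC 0.584, 0.65 against 0.84 (19 points); 0.611, 0.87 against 0.97 (10); 0.638, 0.96 against 1.00 (3); 0.664, under 1 point.
- 13 units per class: true AUC 0.714, 0.32 against 0.61 (29 points); 0.760, 0.46 against 0.77 (30). Part of this comes from the coarse steps of accuracy. With randomised P values the loss for independent scores is at most about 16 points.
- 40 participants x 12 drives, labels permuted within participant: 0 to 23 points at an assumed intraclass correlation (ICC) of 0.3, and 9 to 37 at 0.6.
- A partial simulation that also refits the model leave-one-subject-out: about 5 to 11 points, for example 0.83 for AUC against 0.77 for accuracy.

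**5. Is an AUC pooled over folds a safe replacement?** With pure-noise features and leave-one-subject-out fitting, the pooled AUC averaged 0.48, 0.43 and 0.39 at assumed ICC 0, 0.3 and 0.6, while the within-participant AUC stayed near 0.50. Accuracy was biased too, but less (0.491, 0.460, 0.426). A pooled AUC must therefore not be read against 0.5.

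**The case against.** The strongest defence is that the task is set as two-class classification in a preliminary, exploratory study. The four metrics are conventional for that task, no stated objective promises calibrated probabilities, and the probability wording stands only in the Discussion, partly as an aim. That limits the weight of the point. It does not remove it: the metric list carries no opening word, whereas the list of extra classifiers does, and the Discussion does tell readers that a probability is forecast.

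Three stronger readings are tempting but not supported.
- *The chance test loses 15 points of power.* The article names neither the permutation statistic nor an effect size, unit or sidedness. Fifteen points is a mid-power value for ideal normal scores. The loss nearly vanishes at a true AUC of about 0.64 or more with 320 independent drives, and is larger with few units or strong clustering.
- *The metrics treat a missed impaired driver and a false alarm as equally costly.* Precision and recall describe different errors, and no 0.5 cut is fixed. What stands is that they describe a single operating point.
- *Adding calibration would validate the real-world probability of impairment.* If the middle third of SDLP is dropped, the classes are selected on the outcome and the share of Poor drives is forced to about one half, so calibration there does not carry over to all drives.

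**Conclusion.** The point holds. As written, the evaluation cannot test the forecast probability described in the Discussion, and it does not assess ranking across cut-offs. This follows from the definitions of the metrics and needs no assumption about power.

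The power loss is real in direction only if the permutation statistic is one of the listed metrics, which is the natural reading but is not stated. Its size is 13 to 17 points asymptotically when an AUC test would have 60-90% power, about 5 to 11 points with leave-one-subject-out fitting simulated, and about 0 to 37 points over all assumptions tried. All of these rest on assumed score distributions and intraclass correlations. The point deserves correction before results are reported; it does not invalidate the classification analysis itself.

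**What to change.** In *Predictive Models Using Resting State EEG*:

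1. Add a threshold-free measure on held-out predictions: the AUC computed within each participant and averaged. A pooled AUC is acceptable only if judged against its permutation null and never against 0.5. Participants whose drives all fall in one class contribute nothing to the within-participant AUC; report how many there are. If each participant carries one label, only the pooled form is available.
2. Add a Brier score or log loss on the same predictions.
3. Name that AUC as the permutation statistic, permute labels within participant, and bootstrap by participant.
4. Keep accuracy, precision, recall and F1 as descriptions at a cut fixed in the nested validation set.
5. Report calibration only for the drives actually classified. State that, if the middle third of SDLP is dropped, it does not apply to all drives.

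If the probability is not to be evaluated, reword the two Discussion passages to claim classification of good versus poor performance rather than a forecast probability.

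The cost is analysis wording and a few lines of code on predictions that most of the models already produce. The article says analysis is still under way, and no new data are needed. The support vector machine needs a score output, and calibration may look less favourable than accuracy.

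### The SDLP classes are built to be about equal in size, so the pooled macro-versus-weighted comparison cannot assess sensitivity to imbalance, and precision and F1 hold only for that constructed mix

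*Protocol article*

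**What the plan says.** The Predictive Models Using Resting State EEG section takes SDLP as the main behavioural target and forms two classes: "Good Performance” and “Poor Performance” based on the 33rd and 66th percentiles of the SDLP distribution". It states the consequence for class size: "This percentile-based approach ensures approximately balanced class sizes". It does not say what happens to drives between the two cut points.

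Testing holds out one participant at a time: "A leave-one-subject-out cross-validation strategy will be applied to provide a robust evaluation under intersubject variability". The metrics are accuracy, precision, recall and F1, "reporting both macroaveraged and weighted-averaged metrics to account for potential class imbalance", with the purpose given as: "Comparing these metrics allows assessment of classifier sensitivity to imbalanced classes". The section does not say whether metrics are pooled over all held-out drives or computed fold by fold, and it ranks no metric above the others.

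The Discussion (Implications for the World of Work and Transport) describes the intended use as an approach that "forecasts the probability of optimal or impaired performance due to sleepiness prior to the initiation of a driving task".

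**The concern.** The two statements do not fit together. One says the class sizes are made about equal; the other offers, as a check on imbalance, a comparison that has content only when they are unequal. A report that macro and weighted values agree would look like evidence of robustness, although the agreement follows from how the classes were cut.

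The same cut fixes the share of Poor drives near one half, and precision and F1 depend on that share. Because the Discussion describes a forecast made before a drive, a reader may take the reported precision as the chance that a Poor forecast is right. That holds only where about half the drives are Poor. The share may also differ inside the study, since blocks run from the morning after a laboratory night to the early hours under total sleep deprivation. One pooled precision would hide this.

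**Working it through.** **Inputs**
- Participants: "this number has been arbitrarily set to 40 healthy volunteers" (Sample Size Calculation).
- Drives: one per block, read from "One block of tests is 4 hours long and includes, in a fixed order, a driving simulation" (Experimental Session 1).
- Blocks: 3 in session 1, then 6 and 3 in session 2, so 12 per participant. Drives: 40 × 12 = 480.
- Cut points: 33rd and 66th percentiles.
- Sensitivity, specificity and shares of Poor drives other than the constructed one: assumed, because the article gives none.

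**Step 1: reproduce the stated balance.** Of 480 distinct ordered values, 159 lie at or below the 33rd percentile (Good), 163 at or above the 66th (Poor), and 158 (33%) in between. Among the classified drives the Poor share is 163 / (159 + 163) = 0.506. The stated balance is therefore reproduced, but only if the middle third is left out. A single cut at the 33rd percentile would put 67% of drives in the upper class, and a single cut at the 66th would put 34% there. Either would contradict the statement on class size.

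**Step 2: gap between the two averages.** Let w be the Poor share and m a per-class metric.
- Weighted = w·m(Poor) + (1 − w)·m(Good)
- Macro = [m(Poor) + m(Good)] / 2
- Weighted − macro = (w − 0.5) × [m(Poor) − m(Good)]

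This is an identity for any classifier. With w = 0.506 and a per-class difference of 0.30, the gap is 0.0062 × 0.30 = 0.0019, or about 0.002. For example, with assumed sensitivity 0.90 and specificity 0.60, the pooled gap is 0.002 for recall, about 0.001 in size for precision and 0.0005 for F1. A clearly lopsided classifier would look insensitive to imbalance.

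**Step 3: single folds.** A held-out participant contributes at most 12 drives, and that mix need not be balanced. In a simulation (500 runs, normal SDLP, middle third dropped, assumed intraclass correlation):

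| Intraclass correlation | Folds 75:25 or worse | Folds with one class only |
|---|---|---|
| 0 | 19% | 1% |
| 0.2 | 48% | 11% |
| 0.4 | 63% | 27% |
| 0.6 | 77% | 47% |

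Macro and weighted values can therefore differ within folds.

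**Step 4: dependence on the share of Poor drives.** For share p, sensitivity se and specificity sp:
- Precision = se·p / [se·p + (1 − sp)(1 − p)]
- F1 = 2 × precision × se / (precision + se)

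With se = sp = 0.75 (assumed):

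| Share Poor (assumed) | Precision | F1 (Poor) | 0.75 / precision |
|---|---|---|---|
| 50% | 0.75 | 0.75 | 1.0 |
| 33% | 0.60 | 0.66 | 1.25 |
| 20% | 0.43 | 0.55 | 1.75 |
| 10% | 0.25 | 0.38 | 3.0 |

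At 20%, for example: 0.15 / (0.15 + 0.20) = 0.43. The pattern is the same at 0.80/0.80, where precision is 0.80, 0.50 and 0.31 at 50%, 20% and 10%.

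Accuracy is p·se + (1 − p)·sp, so it depends on the mix when se and sp differ: at 0.90/0.60 it is 0.75 at 50% Poor and 0.63 at 10%. Recall in each class does not contain p.

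**The case against.** - **Pooling is not stated.** Under leave-one-subject-out testing many folds can be skewed, so it would be wrong to infer that macro and weighted averages can never differ. This stands, and it limits the point to pooled metrics. It does not rescue the sentence, because a skewed fold reflects that participant's mix of drives and is not a designed test of imbalance, and some folds may hold one class only.
- **The balance is stated for SDLP only.** The models also cover vigilance and attention, for which no balanced split is given, and reporting both averages is a sensible general precaution there. This stands; the point is confined to SDLP.
- **No field share is known.** A reader might infer that no real shift has a 50:50 mix, or that precision and F1 are artefacts. The documents support neither. They give no share of poor drives in any setting, Poor is defined relative to this sample, and the target settings involve sleep loss, where the share could be high.
- **Size.** A reader might infer that precision is overstated several-fold in general. In the table above a threefold overstatement needs an assumed share of 10% or less; at 33% it is 1.25-fold.
- **Recall is already planned, and the study is exploratory.** Macro recall is the mean of sensitivity and specificity and does not depend on the share. The article also asks that its limitations be weighed before wider use. Both are true, but neither corrects the purpose claimed for the comparison.
- **Recalculated precision can mislead.** If the middle third is excluded, sensitivity and specificity come from extreme groups, so adjusting the share alone still flatters the model. This stands and is carried into the fix.

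**Conclusion.** The point holds for the SDLP classifier at the pooled level. The classes are about equal by construction, so the macro-versus-weighted gap is about 0.002 even with a 0.30 per-class difference, and the comparison cannot assess sensitivity to imbalance. This rests on dropping the middle third, which the text implies but does not state. If a single cut were used instead, the comparison would have some content but the statement on class size would be wrong.

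Precision, F1 and accuracy are valid for the mix evaluated but do not transfer to another share of Poor drives. The size of the change depends wholly on assumed shares and assumed sensitivity and specificity. The documents do not show what the share would be in use, so no overstatement in the field can be claimed from them.

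**What to change.** 1. For SDLP, remove the statement that comparing macro and weighted averages assesses sensitivity to imbalance. Both averages may still be reported.
2. State how drives between the 33rd and 66th percentiles are handled, and whether metrics are pooled or computed per fold.
3. Make recall in each class (sensitivity and specificity) the lead figures.
4. Report precision and F1 as conditional on the class mix, with values at several stated assumed shares of Poor drives (such as 10, 20, 33 and 50%) and at the share observed in each block type: rested day, day after fragmented sleep, first night of deprivation, and the night after recovery sleep.
5. If the middle third is excluded, say that all these figures, including the recalculated precision, describe extreme groups only and are optimistic for a setting that includes intermediate drives.

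The cost is one small table and a few lines of code, with no new data. Reported precision will look less favourable at the lower shares. The Results section says analysis began in June 2025 and is still ongoing, so the change can still be made, and should be labelled as made after analysis started.
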